### **8.8.8 12-months post-randomisation data collection point**

One week before the 12-month post-randomisation data collection point, the SLT receives an automatic alert that the 12-month data collection point approaches so the SLT can prepare the session.

At the session + or – 2 weeks the 12-months post-randomisation data collection point, the SLT video records a speech sample from the PCWS with the parent and/or the SLT at the beginning of the treatment session. The SLT loads this onto a GDPR-proof platform.

Like in each treatment session, the SLT checks for treatment compliance and treatment fidelity, based on the treatment arm. The description of this procedure is described below. The checklists are added in Appendix 9. The SLT reports any risks.

The parent is asked to video record a conversation with the PCWS at home. The SLT loads this onto a GDPR-proof platform and labels the video recording according to the requirements. No treatment is provided during this conversation. The instructions for the video recording need to be followed.

The parent is also asked to report on their child's stuttering severity based on a 10-point scale with three descriptors only and to report on the satisfaction of the PCWS's communication in everyday speaking situations based on a 9-point scale with two descriptors only.

The SLT also ascertains that the information about the treatment sessions that were scheduled between the 9-month and 12-month data collection points is uploaded in REDCap: the date and duration of each session and the information of the compliance check and treatment fidelity checklist of each session.

For 20% of the PCWS the SLT will be asked to record entire treatment sessions, and to load those video recordings onto a GDPR-proof platform. The SLT will receive an automatic alert by email if video recording is required. To avoid bias, for example, SLTs who would behave differently during the video recording compared to other treatment sessions, they are asked to video record each session during that week if they see  $\geq 3$  PCWS in the study at that time or all treatment sessions during 3 weeks if they see  $< 3$  PCWS

at that time. The instructions for the video recording the treatment session need to be followed (these are different instructions than for video recording the speech sample).

Video analysts will score %SS and SR in the two video recorded speech samples of the PCWS. A video analyst will also check the treatment fidelity of the SLT.

If the PCWS would have moved to the maintenance phase (still part of the treatment), the SLT reports any relapses and prepares the parent(s) for relapse management. Further in the protocol it is explained how they do this (depending on the treatment arm).

#### **8.8.9 18-months post-randomisation data collection point (primary data collection point)**

Two weeks before the 18-month post-randomisation data collection point, the SLT receives an automatic alert that the 18-month data collection point approaches so the SLT can prepare the session.

At the session + or – 2 weeks the 18-months post-randomisation data collection point, the primary data collection point in this trial, the SLT video records a speech sample from the PCWS with the parent and/or the SLT at the beginning of the treatment session. The SLT loads this onto a GDPR-proof platform. The SLT also assesses the PCWS for his/her speech attitude (KiddyCAT).

Like in each treatment session, the SLT checks for treatment compliance and treatment fidelity, based on the treatment arm. The description of this procedure is described below. The checklists are added in Appendix 9. The SLT reports any risks.

The parent is asked to video record a conversation with the PCWS at home. The SLT loads this onto a GDPR-proof platform and labels the video recording according to the requirements. No treatment is provided during this conversation. The instructions for the video recording need to be followed.

Video analysts will score %SS and SR in the two video recorded speech samples of the PCWS.

If the PCWS would have moved to the maintenance phase (still part of the treatment), the SLT reports any relapses and prepares the parent(s) for relapse management. Further in the protocol it is explained how they do this (depending on the treatment arm).

The parent is also asked to complete the EQ-5D-Y proxy 1 and the ISPP-questionnaire on an electronic device (computer or smart phone) within a fortnight. The parent is also asked to report on their child's stuttering severity based on a 10-point scale with three descriptors only and to report on the satisfaction of the PCWS's communication in everyday speaking situations based on a 9-point scale with two descriptors only. This will be automatically scheduled using REDCap and access to the questionnaires is emailed to the parent. The SLT checks in REDCap if the questionnaires were completed by the parent.

The SLT also ascertains that the information about the treatment sessions that were scheduled between the 12-month and 18-month data collection points is uploaded in REDCap: the date and duration of each session and the information of the compliance check and treatment fidelity checklist of each session.

%SS and SR will be scored by the blinded video analysts at a later time.

#### ***8.8.10 2-years post-randomisation data collection point (Follow-up)***

Four weeks before the 2-year post-randomisation data collection point, the SLT receives an automatic alert that the 2-year data collection point approaches so the SLT can prepare the session.

At the session + or – 4 weeks the 2-years post-randomisation data collection point, the SLT video records a speech sample from the PCWS with the parent and/or the SLT at the beginning of the treatment session and loads this onto a GDPR-proof platform. The SLT also asks the parent to video record a conversation with the PCWS at home. The SLT loads this onto a GDPR-proof platform and labels the video according to the requirements. No treatment is provided during this conversation. The instructions for the video recording need to be followed.

Video analysts will score %SS and SR in the two video recorded speech samples of the PCWS.

If the PCWS is still in the maintenance phase (part of the treatment), the SLT reports any relapses and prepares the parent(s) for relapse management. Further in the protocol it is explained how they do this (depending on the treatment arm).

The parent is asked to complete the EQ-5D-Y proxy 1 on an electronic device (computer or smart phone) within 4 weeks before or after the data collection point. The parent is also asked to report on their child's stuttering severity based on a 10-point scale with three descriptors only and to report on the satisfaction of the PCWS's communication in everyday speaking situations based on a 9-point scale with two descriptors only. This will be automatically scheduled using REDCap and access to the questionnaire is emailed to the parent. The SLT checks in REDCap if the questionnaires were completed by the parent.

If the PCWS is still receiving treatment (and is not in Maintenance Phase), the SLT also ascertains that the information about the treatment sessions that were scheduled between the 18-month and the 2-year data collection points is provided: the date and duration of each session and the information of the compliance check and treatment fidelity checklist of each session.

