### **8.8.4 *Each treatment session***

The SLT completes a parent compliance checklist and a treatment fidelity checklist after each treatment session in the three treatment arms. The treatment compliance and fidelity checklists aim at increasing the

fidelity of treatment delivery, but also helps the SLT in delivering the treatment approach as per protocol. The description of this procedure is described below. The checklists are added in Appendix 9.

At one month post-randomisation, for 20% of the PCWS the SLT will be asked to video record entire treatment sessions, and to load those video recordings onto a GDPR-proof platform. The SLT will receive an automatic alert by email message if video recording is required. The instructions for this video recording need to be followed (these are different instructions than for recording the speech sample). To avoid bias, for example, SLTs who would behave differently during the video recording compared to other treatment sessions, they are asked to video record each session during that week if they see  $\geq 3$  PCWS in the study at that time or all treatment sessions during 3 weeks if they see  $< 3$  PCWS at that time. The 20% correspond with two PCWS per site and will be chosen randomly with an equal distribution of the three delivered treatment approaches.

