| KiddyCAT                                                               |                           |                    | x        |                                                                       |                                                                                                                                  |                                               |                                                | x                                              |                                    |                                    |
| Treatment date & duration                                              |                           |                    |          | x                                                                     | x                                                                                                                                | x                                             | x                                              | x                                              | (x)                                |                                    |
| Compliance & treatment fidelity ®                           |                           |                    |          | x                                                                     | x                                                                                                                                | x                                             | x                                              | x                                              | (x)                                |                                    |
| QOL (EQ-5D-Y proxy 1)                                                  |                           |                    | x        | x                                                                     |                                                                                                                                  | x                                             |                                                | x                                              | x                                  | x                                  |

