| Relapse reporting and relapse management                               |                           |                    |          |                                                                       | x*                                                                                                                               | x*                                            | x*                                             | x                                              | (x)                                |                                    |
| Risk assessment                                                        |                           |                    |          | x                                                                     | x                                                                                                                                | x                                             | x                                              | x                                              | x                                  |                                    |

Tx = Treatment; %SS = Percentage syllables stuttered; SR = Severity Rating; CAT = Communication Attitude Test; QOL = Quality of Life; CBQ = Children's Behaviour Questionnaire; ISPP = Impact of Stuttering on Preschoolers and Parents; \*: if applicable, that is, if treatment is not initiated straight away; \* if applicable, that is, if the child is in Maintenance Phase. (x) if applicable, that is, if the child is still seeing the SLT; Underlined & bold (18 months post-randomisation) = primary end point; \*\* performed by the video analysts; a depending on the treatment arm; ® Parent compliance and treatment fidelity checklists are completed for each treatment session; ® Treatment fidelity is also evaluated based on of video that is recorded for 20% of the PCWS (entire treatment session) at 1-, 3-, 6- and 12-months post-randomisation.

Figure 3. Overview of measurements in TreatPaCS

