### 9.1.6 Maintenance phase

The maintenance phase starts when the PCWS and parent(s) achieved the goals of the five phases. Usually the stuttering is reduced to (near) zero stuttering. Treatment sessions to monitor if achieved goals are maintained are scheduled with an interval of 2, 2, 4, 4, 8, 8 and 16 weeks. If necessary, SLTs add extra sessions during maintenance, for example if the goals were not maintained.

During the maintenance sessions, the SLT asks the parent(s) to report about the PCWS and observes the speech of the PCWS. Depending on the speech of the PCWS, a decision is taken:

- The PCWS does not stutter anymore: the parent(s) continues to observe closely but there is no need to re-introduce treatment techniques.
- The PCWS responds with stuttering to stuttering-inducing factors: the parent(s) re-instates specific treatment techniques depending on the situation or the PCWS receives training on certain concepts or skills.
- The PCWS stutters severely: the SLT may decide to re-introduce specific treatment concepts or skills and may ask the parent(s) to implement them at home.

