It is expected that most relapse of stuttering will be treated successfully in the treatment approaches as they all aim for independent managing of relapse of stuttering by the parents. The treatment approaches are also expected to achieve similar outcomes regarding QOL and attitude towards speech.

It is however important to realise that stuttering will persist in a small number of children. When a patient is treated for stuttering at an older age, treatment is much more complicated and takes more time than treatment at a younger age, i.e. before the age of 6 years. We do not want to imply that the existing reimbursement scheme should decrease the number of reimbursed sessions. We think, if the trial shows that direct treatment, and especially the LP, is efficient and a more economical way of delivering the treatment, an extension to the reimbursement of 60-minutes sessions for children <10 years if parents are attending/participate in treatment would be beneficial.

If less treatment sessions are required and if they are grouped to one session per week, the burden upon the family of traveling to the stuttering practice and the risk on a negative impact on the parents' jobs and life will significantly decrease.

To evaluate the economic value of the trial (differences between the three treatment arms), no extra data are required. With the data that are provided in the trial, it is possible to calculate burden (based on number of treatment sessions) and cost of the treatment (based on number and length of sessions). In addition, the time spent implementing the program at home during the week will also be considered. Between the three treatment arms, travel time to the SLT is not expected to be different.

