**Maintenance Phase (Three treatment arms)**

**Date treatment session:** ...../...../.....

**Duration of the treatment session:** 30 / ..... minutes

- ☐ At least one parent attends the treatment session with the child
- ☐ This treatment session is scheduled with an interval of 2/2/4/4/8/8/16 weeks since previous session *(indicate which one applies)*
- ☐ The parent is vigilant and reported any (signs of) relapse in case there was a relapse
- ☐ The parent is able to manage relapse independently

**Compliance Checklist** *(pour vérifier si les parents appliquent le traitement)*

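### Section 8.8.10 exempts children in maintenance from the session-data check for months 18 to 24, contradicting Figure 3 and leaving late sessions to each site's reading

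*Protocol*

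**What the plan says.** All references are to the Protocol.

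- **Section 8.8.10 (2-year visit).** The speech-language therapist (SLT) checks date, duration and checklists of the sessions since month 18 under a condition: "If the PCWS is still receiving treatment (and is not in Maintenance Phase), the SLT also ascertains that the information about the treatment sessions" is provided. The same section describes maintenance as part of the treatment.
- **Section 8.8.9 (18-month visit).** The corresponding instruction has no such condition: "The SLT also ascertains that the information about the treatment sessions that were scheduled between the 12-month and 18-month data collection points is uploaded in" the database.
- **Figure 3.** The row "Treatment date & duration" and the compliance and fidelity row carry a bracketed cross at 2 years. The footnote defines that cross as "x) if applicable, that is, if the child is still seeing the SLT". A child in maintenance is still seeing the SLT.
- **Section 8.8.4.** "The SLT completes a parent compliance checklist and a treatment fidelity checklist after each treatment session in the three treatment arms". Section 8.9.1 has the compliance information uploaded at each data collection point, and section 12.1 has compliance and fidelity data loaded for each session. Appendix 9 contains a compliance checklist headed "Maintenance Phase (Three treatment arms", with its own date and duration fields.
- **Sections 9.1.6, 9.2.6 and 9.3.2.** Seven maintenance sessions are scheduled at intervals of 2, 2, 4, 4, 8, 8 and 16 weeks, and the number is open-ended: "If necessary, SLTs add extra sessions during maintenance, for example if the goals were not maintained".
- **Section 11.4.3.** "To evaluate the economic value of the trial (differences between the three treatment arms), no extra data are required"; burden and cost are to follow from the number and length of sessions. The expected totals of 47, 61 and 94 half-hour units include maintenance (section 4.3.1).
- **Sections 4.2 and 4.3.2.** The secondary endpoint counts hours, weeks and sessions only until maintenance starts.

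**The concern.** Two instructions for the same visit name different children. A site working from Figure 3 uploads every session between months 18 and 24. A site working from 8.8.10 checks only children in active treatment. With 30 private practices entering data, completeness would vary by site.

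Whether a child has sessions in that window depends on when the child reached maintenance and whether stuttering returned, so the omitted sessions would not be a random subset. They would be late maintenance sessions and sessions added because goals were not maintained. These belong to the resource use that section 11.4.3 says can be costed from the trial data as they stand.

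The wording also leaves open when maintenance status is judged. If it is judged at the 2-year visit, a child who was in active treatment at month 18 and moved to maintenance before month 24 falls outside the check altogether. That child's active sessions after month 18 belong to the secondary endpoint.

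**Working it through.** **1. The plan's own cost figures.** Payer cost per child (section 11.4) is EUR 1000.2 for LP, 1299.1 for Mini-KIDS and 1660.9 for SCBT; section 11.4.3 uses 677 children per year.

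- LP vs SCBT: 677 × (1660.9 − 1000.2) = 447,293.90; stated 447,280.38.
- Mini-KIDS vs SCBT: 677 × (1660.9 − 1299.1) = 244,938.60; stated 244,938.60.
- LP vs Mini-KIDS: 677 × (1299.1 − 1000.2) = 202,355.30; stated 202,341.76.

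All agree within 0.01%, so the projected savings do rest on totals that include maintenance. Total cost per half-hour unit is 1264.7/47 = EUR 26.91 (LP), 1642.6/61 = 26.93 (Mini-KIDS) and 2103.9/94 = 22.38 (SCBT).

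**2. Scheduled maintenance sessions in the window.** The intervals add up to weeks 2, 4, 8, 12, 20, 28 and 44 after entry at week S. Month 18 is 18 × 365.25/12/7 = week 78.27; month 24 is week 104.36. The count is of sessions with 78.27 < S + offset ≤ 104.36. The last session passes month 18 once S > 78.27 − 44 = 34.27.

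| Entry week S | Sessions in window (week) | Not checked under 8.8.10 |
|---|---|---|
| 34 | none (last at 78) | 0 |
| 42 | 86 | 1 |
| 52 | 80, 96 | 2 |
| 60 | 80, 88, 104 | 3 |
| 76 | 80, 84, 88, 96, 104 | 5 |
| 76.3 | 78.3, 80.3, 84.3, 88.3, 96.3, 104.3 | 6 |

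Under Figure 3 the last column is 0 throughout.

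**3. Where the expected medians fall.** Assumptions, because the protocol does not split its totals: screening 1–2 units; baseline 3 units (LP, SCBT) or 4 (Mini-KIDS); parent sessions 0 units (LP), 0–4 (Mini-KIDS), and 0 or 16–20 (SCBT, the latter being 8 to 10 one-hour sessions); maintenance 7 units; no missed weeks. In LP and Mini-KIDS the first six sessions use 12 units in 6 weeks.

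- LP: 47 − 7 − 3 − (1 to 2) − 12 = 23 to 24 further weekly units; entry at week 29 to 30; **0 lost**.
- Mini-KIDS: 61 − 7 − 4 − (1 to 2) − (0 to 4) − 12 = 32 to 37; entry at week 38 to 43; **1 lost**, about EUR 27, or 1/61 = 1.6% of the total.
- SCBT, twice weekly: 94 − 7 − 3 − (1 to 2) = 82 to 83 units without parent sessions, entry at week 41 to 41.5, **1 lost** (about EUR 22, 1/94 = 1.1%); with 16–20 parent units, 62 to 67 units, entry at week 31 to 33.5, **0 lost**.

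Entry at week 76 loses 5 units, at most 5 × 26.93 = EUR 135 for that child. Stated differences in mean total cost are 1642.6 − 1264.7 = EUR 377.9 and 2103.9 − 1642.6 = EUR 461.3, but the two scales are not directly comparable: the first is per affected child, and the share of children affected is not given.

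**4. Entry between months 18 and 24, with status judged at the 2-year visit.** Active weeks after month 18 are S − 78.27. At S = 92 that is about 14 weekly or 27 twice-weekly sessions; at S = 103, about 25 or 49. The Trial Summary allows treatment of up to 2 years, so such children can occur; their number is not given.

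**The case against.** The strongest reply is that the clause in 8.8.10 is a completeness check and does not prohibit uploading maintenance sessions. Sections 8.8.4, 8.9.1 and 12.1, Figure 3 and the maintenance checklist all point towards documenting and loading every session. Everything up to month 18, maintenance included, is explicitly collected. The time-to-treatment-goal endpoint stops at the start of maintenance, total sessions to 24 months is not a listed endpoint, and section 11.4 sets no 24-month horizon. Relapses in maintenance are still reported at 2 years.

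Most of this stands, and it rules out two stronger readings that a reader might infer.

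- *That total sessions and cost cannot be derived.* The each-session records exist, all data to month 18 are requested, and the scheduled shortfall at the expected medians is 0 to 1 session.
- *That the slower programs are systematically undercounted.* SCBT, with the most units, is expected to lose 0 to 1 session and Mini-KIDS 1. Children still in active treatment at 2 years are fully covered by 8.8.10. The loss therefore does not increase steadily with slowness.

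The reply does not remove the contradiction. The upload is tied to the data collection points, and 8.8.10 is the instruction for this one. A site that follows it has been told to check a narrower group than Figure 3 names. The general rules also cover the active sessions in step 4, so that loss is a possibility under one reading and not an established consequence.

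**Conclusion.** The point holds as an internal contradiction with a modest, site-dependent consequence. Read literally, 8.8.10 leaves unchecked the maintenance and added relapse sessions after month 18 of children who enter maintenance after about week 34. The scheduled part is 0 to 1 session at the expected medians, at most about 2% of cost, and 5 to 6 sessions for entry just before month 18. Added relapse sessions come on top, in unknown number. The larger exposure, up to about 25 weekly or 50 twice-weekly active sessions in a child who enters maintenance close to month 24, arises only if status is judged at the 2-year visit; it would reach the secondary endpoint of hours and sessions until maintenance.

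The loss is related to course of response, so the cost and burden comparison would be somewhat incomplete, and section 11.4.3's assurance is secure only if Figure 3 governs. The entry weeks depend on the assumed split of the 47, 61 and 94 units. Without the distribution of entry times and relapse sessions, neither an arm-level bias nor its direction can be stated.

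**What to change.** In section 8.8.10, delete the parenthesis that excludes children in the maintenance phase, and use Figure 3's criterion: date, duration and checklists of every session between months 18 and 24, including maintenance and added relapse sessions, are uploaded for any child still seeing the SLT. This also removes the question of when maintenance status is judged. In section 11.4, state the time horizon of the cost comparison.

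The cost is one clause and one sentence. The checklists are already completed after each session and a maintenance version exists, so sites add only the upload. Correcting this later would mean retrieving records from up to 30 private practices.
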